## Abstract

**Background:**

Early blood transfusion improves survival in patients with life-threatening bleeding, but the optimal transfusion strategy in the pre-hospital setting has yet to be established. Although there is some evidence of benefit with the use of whole blood, there have been no randomised controlled trials exploring the clinical and cost effectiveness of pre-hospital administration of whole blood versus component therapy for trauma patients with life-threatening bleeding. The aim of this trial is to determine whether pre-hospital leukocyte-depleted whole blood transfusion is better than standard care (blood component transfusion) in reducing the proportion of participants who experience death or massive transfusion at 24 h.

**Methods:**

This is a multi-centre, superiority, open-label, randomised controlled trial with internal pilot and within-trial cost-effectiveness analysis. Patients of any age will be eligible if they have suffered major traumatic haemorrhage and are attended by a participating air ambulance service. The primary outcome is the proportion of participants with traumatic haemorrhage who have died (all-cause mortality) or received massive transfusion in the first 24 h from randomisation. A number of secondary clinical, process, and safety endpoints will be collected and analysed. Cost (provision of whole blood, hospital, health, and wider care resource use) and outcome data will be synthesised to present incremental cost-effectiveness ratios for the trial primary outcome and cost per quality-adjusted life year at 90 days after injury. We plan to recruit 848 participants (a two-sided test with 85% power, 5% type I error, 1-1 allocation, and one interim analysis would require 602 participants—after allowing for 25% of participants in traumatic cardiac arrest and an additional 5% drop out, the sample size is 848).

**Discussion:**

The SWiFT trial will recruit 848 participants across at least ten air ambulances services in the UK. It will investigate the clinical and cost-effectiveness of whole blood transfusion versus component therapy in the management of patients with life-threatening bleeding in the pre-hospital setting.

**Trial registration:**

ISRCTN: 23657907; EudraCT: 2021-006876-18; IRAS Number: 300414; REC: 22/SC/0072, 21 Dec 2021.

## Administrative information

Note: the numbers in curly brackets in this protocol refer to SPIRIT checklist item numbers. The order of the items has been modified to group similar items (see http://www.equator-network.org/reporting-guidelines/spirit-2013-statement-defining-standard-protocol-items-for-clinical-trials/).

## Introduction

### Background and rationale {6a}

Major trauma kills more than 5400 people every year in the UK [1] and globally more than human immunodeficiency virus-acquired immunodeficiency syndrome (HIV-AIDS), tuberculosis (TB), and malaria combined [2]. Uncontrolled bleeding accounts for a significant proportion of these deaths, with approximately 20% occurring in the first 24 h and 40% occurring within the first 30 days [3, 4]. Blood transfusion is a life-saving treatment in the management of bleeding until it is controlled in hospital by surgery or interventional radiology. Blood transfusion is delivered through different blood components, namely red blood cells (RBC), plasma, and platelets; all these components are derived from whole blood (WB) donation and are stored separately at different temperatures.

Observational studies in military [5] and civilian [6] settings have reported a 12–14% absolute reduction in 30-day mortality with pre-hospital RBC transfusion, with the effect being greater if transfusion is started within 15 min of medical evacuation [5]. However, recent trials investigating the use of pre-hospital blood transfusion have shown conflicting results. The RePHILL trial showed no benefit in a composite primary outcome of lactate clearance and episode mortality from transfusion with RBC plus lyophilised plasma when compared to resuscitation with normal saline [3]. Two US trials investigating the use of pre-hospital plasma resuscitation also showed conflicting results [7, 8], although combined data from these trials suggest that there is survival benefit, which is greatest in patients who received both RBC and plasma [9], in patients with blunt trauma [10], and when pre-hospital times are longer (than 20 min) [11].

In the UK, many patients who are bleeding at the scene of an incident are transfused blood before they arrive at hospital. This is most commonly a combination of RBC and plasma [4]. In a national survey in 2020, of the 18 UK Air Ambulance Services that responded, 67% administered red blood cells (RBC) and plasma, 22% administered RBC only, and 11% plasma only [12]. In this survey, over 80% stated that WB would be their preferred component, but the evidence for its use is limited.

Systematic reviews, comparing the impact of WB transfusion versus blood component therapy on 24-h and 30-day mortality for adult trauma patients with acute major haemorrhage, showed no clear benefit with WB transfusion [13–15]. In these reviews, there was only one randomised controlled trial (*n* = 107 patients), which was not powered to demonstrate a difference in survival. Since the publication of these systematic reviews, an observational study in the USA comparing WB to component therapy (RBC and or plasma) reported a twofold increase in likelihood of 30-day survival with WB transfusion (odds ratio, 2.19; 95% CI 1.01–4.76; *p* = 0.047) [16].

The optimal blood transfusion strategy in the pre-hospital setting has yet to be established. The implementation of WB into routine practice would result in significant changes to the current manufacturing processes for the blood services and potentially increased cost. Although there is some evidence of benefit with the use of WB, there have been no prospective randomised controlled trials exploring the clinical and cost effectiveness of pre-hospital administration of WB versus component therapy for bleeding trauma patients. It is therefore essential for patients, healthcare professionals and blood services that the clinical and cost effectiveness of pre-hospital WB transfusion is evaluated in a large trial before its widespread implementation in the NHS.

### Objectives {7}

The primary objective is to determine whether pre-hospital leukocyte-depleted whole blood transfusion is better than standard care (component transfusion) in reducing the proportion of participants who experience death or massive transfusion at 24 h. The secondary objectives are to determine all-cause mortality at 6 h, 24 h, 30 days, and 90 days; morbidity up to 30 days (number of organ failure-free days, number of days in critical care and in hospital); hospital resource use up to 30 days, discharge, or death, including organ failure-free days, time spent in critical care and total in-patient stay, blood components, and additional haemostatic agents received; cost-effectiveness; and safety.

### Trial design {8}

The trial design is a multi-centre, pragmatic, superiority, randomised controlled, open-label, parallel group, two-arm trial with internal pilot and within-trial cost-effectiveness analysis.

## Methods: participants, interventions, and outcomes

### Study setting {9}

Air Ambulance Services (AAS) are responsible for treating patients on scene and delivering the trial intervention prior to hospital admission. These sites will be Air Ambulance Services in the UK that deliver a combination of RBC and plasma as standard care for the treatment of life-threatening bleeding.

Transfusion laboratory sites are responsible for supplying blood components in accordance with the randomisation procedure. These sites are the hospitals (transfusion laboratories) that supply blood components to the participating Air Ambulance Services.

Receiving hospital sites are secondary care sites where participants will be admitted following pre-hospital trial treatment. These sites will be designated major trauma centres, trauma units, or other hospitals that receive patients from the participating Air Ambulance Services.

### Eligibility criteria {10}

The pragmatic nature of this trial means that the decision to administer the intervention will be based on clinician judgement and according to the AAS usual criteria for initiation of blood transfusion. As injured children and adults are routinely managed by Air Ambulance Services and may receive pre-hospital blood transfusion, patients of all ages will be included in the study. Inclusion criteria are therefore a patient (of any age) who has suffered a traumatic injury, is attended by a participating Air Ambulance Service clinical team, and who requires pre-hospital blood transfusion to treat major traumatic haemorrhage. Exclusion criteria are inability to achieve intravenous or intraosseous access; if it is known that a patient will object to being given blood transfusion for any reason; or if blood has already been administered on-scene, prior to arrival of the participating AAS.

### Who will take informed consent? {26a}

Participants will be enrolled under an emergency waiver of consent.

Major traumatic haemorrhage is a life-threatening condition that requires urgent treatment. The vast majority of participants will lack capacity and/or will be minors of unknown age. Due to the emergency nature of major trauma, time will not allow for written informed consent to be obtained prior to the intervention being administered. Therefore, it would be inappropriate to attempt to gain informed consent at this time, as it could delay life-saving treatment. It would also be clinically unjustifiable to delay treatment until full informed consent can be obtained from a personal legal representative or parent/guardian. Even if such a representative or person with parental responsibility were immediately available, the emotional distress of the situation is such that they would be unlikely to make an informed decision in the minimal time available.

Consequently, participants will be enrolled under an emergency waiver of consent. Participants who are incapable of giving consent in emergency situations are an established exception to the general rule of informed consent in clinical trials. This is acknowledged in the Declaration of Helsinki, 2013. Under UK law (The Medicines for Human Use (Clinical Trials: Amendment No. 2) Regulations 2006), minors or incapacitated adults in emergency settings can be entered into a trial before informed consent is obtained.

Contact with trial participants and/or their relatives/friends/person with parental responsibility to initiate the consent process will be made by the local research team at the receiving hospital as soon as practically possible after the initial emergency has passed. Details of the informed consent discussions will be recorded in the participant’s medical notes.

In exceptional circumstances, it may not be possible to obtain informed consent (either via the participant directly, or via a personal/professional legal representative) before a participant is discharged from hospital. If no contact with the participant is possible, we will use the data that has previously been collected under the provisions of Section 251 of the National Health Service Act 2006 (with approval from the Confidentiality Advisory Group (CAG)).

### Additional consent provisions for collection and use of participant data and biological specimens {26b}

Some receiving hospital sites are taking part in the Activation of Coagulation and Inflammation in Trauma 2 (ACIT-2) study, which involves collection of research blood samples after arrival at hospital. The arrangements for consent are described in the ACIT-2 study protocol.

## Interventions

### Explanation for the choice of comparators {6b}

The trial will compare up to two units of WB (intervention arm) versus up to two units of RBCs and two units of plasma (control arm). Following this, additional blood components will be administered as required (as per standard of care). The choice of control intervention was determined by the results of a national survey of air ambulances, conducted in 2020, which found that the majority of patients requiring pre-hospital transfusion in the UK receive a combination of RBCs and plasma [12].

### Intervention description {11a}

Eligible patients will receive either WB or a combination of RBC and plasma, delivered via an intravenous cannula or an intraosseous cannula, in the pre-hospital environment by the attending air ambulance service clinical team. If the transfusion is still in progress when the patient arrives at hospital, it can be continued until complete if it is still clinically indicated. Once complete, routine care will continue, including further blood products as per local protocol.

The WB component will be manufactured by NHS Blood and Transplant, which is the main blood supplier of blood in England. The WB units are derived from a single donor after the WB is collected into 66.5-mL citrate-phosphate-dextrose (CPD) anticoagulant and filtered to remove white cells [17, 18], as a variant Creutzfeldt–Jakob disease (CJD) safety measure step that is applied to all blood components manufactured in the UK since 1999.

Once manufactured, the WB units will be transported to hospitals under continuous temperature control as per standard operating procedures and stored in the transfusion laboratories at 2–6 °C for up to 21 days [17, 18]. The WB units will be group O, RhD negative, high titre negative for anti-A and anti-B, and Kell negative.

The control arm will consist of 2 units of RBC and 2 units of plasma (either thawed fresh frozen plasma, FFP, up to 5 days post-thawing or freeze-dried plasma (LyoPlas) [19, 20], dependent on the standard practice for each AAS. RBC and FFP are blood components that are supplied by NHS Blood and Transplant to the hospitals that are supporting this trial. LyoPlas is a freeze-dried plasma product derived from a single donation and is licenced for use in the same indication as FFP.

### Criteria for discontinuing or modifying allocated interventions {11b}

If the trial intervention has not been completed by the time the participant arrives in hospital, it should be completed after arrival at hospital if it is still clinically indicated. Further management is dictated by normal clinical protocols. If bleeding continues and further fluid resuscitation is needed, additional blood components will be administered as per standard care and as required, following the initial trial components. All blood components will be given according to local standard policies on the use of blood warmers.

### Strategies to improve adherence to interventions {11c}

The volume of blood product given will follow local protocol. For adult patients, this would usually be up to two units of WB or up to two units each of RBCs and plasma. For children, local protocol will be followed regarding the comparable number of units that should be received.

### Relevant concomitant care permitted or prohibited during the trial {11d}

WB, RBC, and LyoPlas are stored in citrate; therefore, solutions containing calcium will not be administered concurrently through the same cannula. Medicinal products should not be added to WB, RBC, thawed plasma, or LyoPlas. No other blood products (e.g. fibrinogen concentrate) should be given in the pre-hospital phase of care.

Due to the emergency nature of this trial, it is highly unlikely that those enrolling participants to SWiFT will be aware if a participant is already enrolled in a clinical trial. Where a SWiFT participant is subsequently found to have been participating in a concurrent trial or is being considered for enrolment into another trial, the site must notify the SWiFT CIs, who will in turn liaise with the CI for the other trial to determine whether co-enrolment is permitted.

### Provisions for post-trial care {30}

After the trial intervention is delivered, all further management will be according to standard local protocols. No specific provisions for post-trial care have been made.

### Outcomes {12}

The primary outcome is the proportion of participants who have died (all-cause mortality) or received massive transfusion in the first 24 h from randomisation. A participant is considered randomised and entered into the trial when the trial intervention box has been opened.

For the purposes of analysis, two units of whole blood will be counted as equivalent to four total units due to the volume difference between the intervention and control arm, the fact that two units of whole blood contain the equivalent of two units of plasma plus two units of packed RBCs, and for the massive transfusion part of the primary analysis, both arms will start will an equal baseline.

Secondary outcomes include the following: the proportion of participants who received massive transfusion (for adults, a total of 10 or more units of any blood components) in the first 24 h from randomisation; all-cause mortality at 6 h, 24 h, 30 days, and 90 days from randomisation; number of organ failure-free days up to 30 days, defined as the number of days free of advanced cardiovascular, advanced respiratory, and advanced renal support; days in critical care and separately in an acute care hospital (up to 90 days); units of each blood component received in the 24 h after randomisation, including pre-hospital transfusions (WB, RBC, plasma, platelets, and cryoprecipitate); amount of cell salvage received at 24 h (in ml) after randomisation; number of participants receiving additional haemostatic agents received at 24 h after randomisation (recombinant factor VIIa, fibrinogen concentrate, prothrombin complex concentrate (PCC), tranexamic acid (TXA)); presence of coagulopathy (defined as prothrombin time above the normal range) in the first sample taken on arrival at an acute care hospital; acid-base disturbance measured by lactate, base excess, and pH level in first sample taken on arrival at acute care hospital; cost of provision of the whole blood intervention; hospital resource use up to discharge or death, including ventilator days, days spent in critical care, and total in-patient stay; health, social, and wider care service resource use to 90 days after injury; health-related quality of life (EuroQol 5 Dimension 5 Level, EQ-5D-5L) at 90 days after injury; thrombosis (arterial and venous) up to 30 days after randomisation or hospital discharge or death, whichever is first; and all transfusion reactions/events relating to pre-hospital blood components which have been reported to SHOT (Serious Hazards of Transfusion) in the first 14 days after randomisation.

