#### Primary outcome

The primary outcome will be determined as the proportion of participants who have either died (from all causes) or received 10 or more units of blood components, within the 24 h from randomisation (a participant is considered randomised and entered into the trial when the trial intervention box has been opened). The following will be included in the blood component count: RBC, platelets, whole blood, thawed plasma (or LyoPlas), and cryoprecipitate. In this trial, for the purposes of analysis, two units of whole blood will be counted as equivalent to four total units due to the volume difference between the intervention and control arm, the fact that two units of whole blood contain the equivalent of two units of plasma plus two units of packed RBCs, and for the massive transfusion part of the primary analysis, both arms will start will an equal baseline. The composite outcome will be analysed using a mixed logistic regression model with adjustment for AAS, fitted as a random effect. A superiority hypothesis will be tested and the results from the adjusted analysis will be considered the primary analysis.

All analyses will be performed on a modified intention to treat basis, to exclude participants who experience a traumatic cardiac arrest, but will include all other randomised patients on whom a value of the response variable has been obtained, including those randomised in error and regardless of the participants’ adherence to the protocol. The data will be presented and analysed according to the arm to which the participant was randomised, regardless of whether they received the randomised intervention or not.

The primary outcome will be replicated per protocol, which will exclude participants who experience a traumatic cardiac arrest, those who experience a protocol deviation, were randomised in error or were withdrawn from the trial. The data will be presented and analysed according to the arm to which the participant was randomised.

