#### Secondary outcome analysis

All-cause mortality at 6 h, 24 h, 30 days, and 90 days, the proportion of participants who receive 10 or more units of any blood components, and presence of coagulopathy will each be analysed separately using the same model that is described for the primary outcome.

Organ failure-free days and days in critical care and an acute care hospital will be reported as a median and IQR, by treatment arm and overall.

Units of each blood component received in the 24 h after randomisation will be summarised with a median and interquartile range and analysed using a negative binomial model, with adjustment for AAS.

Amount of millilitres (ml) of cell salvage at 24 h after randomisation and lactate, base excess, and pH level in first sample taken on arrival at acute care hospital will be analysed separately using a mixed linear regression model, with adjustment for AAS.

For each of the additional haemostatic agents, the number of participants who received each agent will be presented by trial arm and overall.

Thrombosis (arterial or venous thrombosis) up to 30 days after randomisation (or death or hospital discharge, whichever is first) and transfusion reactions/events relating to pre-hospital blood components which have been reported to SHOT (Serious Hazards of Transfusion) occurring in the first 14 days after randomisation will be summarised.

The economic evaluation will establish the resources required to provide the whole blood intervention, estimate intervention as compared to standard care costs, and conduct a full incremental cost-effectiveness analysis. Analyses will be undertaken against a primary perspective of the NHS/Social Care. Cost and outcome data will be synthesised to present incremental cost-effectiveness ratios for the primary outcome and cost per quality-adjusted life-year at 90 days. Multivariable regression analyses and bootstrapping will be employed, uncertainty will be explored, and cost-effectiveness acceptability curves will be presented. The internationally recognised CHEERs guidelines will be followed, and planned analyses will be described in a health economics analysis plan, which will be fully concordant with the SAP.

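### The between-arm models for RBC and plasma units count the randomised box units, so they favour whole blood even if later transfusion is identical

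*Protocol article*

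**What the plan says.** All references are to the protocol article.

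- **Outcome.** Outcomes {12} has as a secondary outcome the number of units of each component given within 24 h of randomisation, "including pre-hospital transfusions (WB, RBC, plasma, platelets, and cryoprecipitate"). Whole blood, RBC and plasma are separate categories.
- **Start of the window.** The same section states: "A participant is considered randomised and entered into the trial when the trial intervention box has been opened". Box units therefore fall inside the 24 h.
- **Contents of the box.** Explanation for the choice of comparators {6b} compares "up to two units of WB (intervention arm) versus up to two units of RBCs and two units of plasma (control arm").
- **Model.** Under Secondary outcome analysis, these counts are summarised by median and interquartile range and "analysed using a negative binomial model, with adjustment for AAS".
- **Conversion rule.** In Outcomes {12}, and again under Primary outcome, "two units of whole blood will be counted as equivalent to four total units". One reason given is that "for the massive transfusion part of the primary analysis, both arms will start will an equal baseline".
- **After the box.** Under Criteria for discontinuing or modifying allocated interventions {11b}, "additional blood components will be administered as per standard care and as required, following the initial trial components". This applies to both arms.

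**The concern.** A comparison of RBC or plasma units between the arms should tell the reader whether whole blood changes the need for those components. As defined, each count is the sum of two parts: the units in the allocated box and the units given afterwards. The first part is fixed by randomisation. It adds up to two RBC and two plasma units to each control patient, and none to a patient given the whole-blood box.

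The Discussion raises the possibility that early whole blood reduces further component transfusion in hospital. Sample size {14} cites an observational study with fewer RBC and plasma units after the emergency department. Readers will look to these models for evidence on that question, and the models as defined cannot supply it.

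The whole-blood count has the mirror-image problem. Whole blood is not described as part of standard care, so the expected control count is about zero.

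**Working it through.** **1. Size of the comparison.** The article states no figure for this outcome. The only figure that can be reproduced is the sample size, which sets the scale of the simulations. For 68% vs 56%, two-sided 5% and 85% power, the usual formula gives 293 per arm (586 in total), or 309 per arm (618) with continuity correction. The stated 602 lies between these. Inflation gives 602/(0.75 × 0.95) = 845, against the stated 848. I accept both figures and use 602/2 = 301 per arm.

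**2. Expected rate ratio with no true effect.** Let m be the mean later units of RBC (or plasma) per patient, equal in both arms, and b the mean box units of that component per control patient. Then

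ratio (whole blood vs control) = m/(m + b).

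The article limits b to 2 and does not give m. I take m = 2 to 8 as an **assumption**.

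| m | b = 2 | b = 1.7 |
|---|---|---|
| 2 | 2/4 = 0.50 | 2/3.7 = 0.54 |
| 4 | 4/6 = 0.67 | 4/5.7 = 0.70 |
| 6 | 6/8 = 0.75 | 6/7.7 = 0.78 |
| 8 | 8/10 = 0.80 | 8/9.7 = 0.82 |

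For any b above 0 the ratio is below 1 at every finite m.

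**3. How often the model would reject.** I used simulated negative binomial fits with 301 per arm, no true effect and arm as the only covariate. Later units were gamma-Poisson with shape 1, which is also an assumption.

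| m | Median ratio (b = 2) | p<0.05 |
|---|---|---|
| 2 | 0.50 | 100% |
| 4 | 0.66 | 100% |
| 6 | 0.75 | 98.5% |
| 8 | 0.81 | 81% |

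A separate set with shape 0.8 and b = 2 gave 100%, 100% and 78% at m = 2, 4 and 8. With b = 1.7, rejection ran from 68% to 100% at shape 1 and from 53% to 100% at shape 0.5; the lowest values are at m = 8. These runs assume that every patient receives the allocated box. Patients in the whole-blood arm who received RBC and plasma instead would dilute the artefact.

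**4. Does the definition cause it?** The same set-up with b = 2 and the count changed gives:

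| Count modelled | Median ratio | p<0.05 |
|---|---|---|
| Box units left out | 0.99 to 1.01 | 4% to 7% |
| Each whole-blood unit counted as 1 RBC + 1 plasma | 1.00 to 1.01 | 5% to 11% |

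Both remove the shift. The second is not perfectly calibrated.

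**5. Whole-blood units.** With no control patient given whole blood, the log rate ratio runs to the boundary (21 to 26, depending on the fit), and its standard error is undefined or about 14,600. With 1, 5 or 15 control patients given whole blood, a fit with fixed dispersion returns log ratios of 5.5, 3.9 and 2.8 (standard errors 0.71, 0.33 and 0.20). The result follows the number of deviations. The full negative binomial fit gave no valid standard error in any of these cases: counts of 0 to 2 in the treated arm are underdispersed (variance/mean about 0.14).

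**The case against.** **The conversion rule may already cover this.** It is introduced as applying to analysis in general and stands ahead of the secondary outcomes. One of its reasons is that two whole-blood units contain the equivalent of two plasma and two RBC units. Only the last reason mentions massive transfusion. This has some force: the sponsor recognised the imbalance, and a later plan could extend the rule. But the rule yields a number of total units, and the secondary outcome still lists whole blood as its own component. On the wording, the RBC and plasma models are not corrected.

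**It may be only analysis-plan detail.** A conversion rule for a secondary count can be left to the analysis plan. Here, however, the article states both the count and the model, and together they give a misleading contrast.

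**Total consumption is a legitimate quantity.** This stands. Objectives {7} places blood components under resource use, and the Discussion treats donor supply as a central issue. Fewer RBC and plasma units because whole blood replaced them is real consumption. A reader might infer that counting box units is an error in itself. The documents do not support that. The fault lies in testing the count between the arms as if it measured later need.

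**The size rests on assumed inputs.** This also stands. Neither m nor the dispersion is in the article, and the simulations omit the adjustment for air ambulance service. A reader might infer that the trial is certain to report significantly lower RBC and plasma use and to present it as benefit. The documents support the direction of the shift, but not a certain p-value or how the sponsor will interpret the result.

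**Conclusion.** The concern holds for the RBC and plasma models. Their expected ratio under no effect on later transfusion is m/(m+2) with two box units per control patient: about 0.50 to 0.80 for an assumed m of 2 to 8, with p<0.05 in roughly 80% to 100% of simulated trials. With fewer box units and heavier dispersion, the rejection rate falls to about 53%. The direction follows from the text alone; the size depends on the assumptions. These contrasts cannot show reduced downstream transfusion.

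A reader might infer that the whole-blood model can never be estimated. That is true only if no control patient receives whole blood. Analysis is as randomised, so a few deviations would give a finite ratio, but one that reflects only those deviations.

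A reader might also infer that the primary result is at risk. It is not: the primary composite and the massive-transfusion count use total units, to which the conversion rule applies. Platelet and cryoprecipitate counts are not shifted by the listed box contents. This is a should-fix point on one secondary outcome.

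**What to change.** In Outcomes {12} and Secondary outcome analysis, or in the analysis plan before any unblinded comparison:

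1. For the inferential RBC and plasma models, state one of two counts: (a) each whole-blood unit counts as one RBC plus one plasma, which is the existing equivalence applied per component; or (b) units other than the trial-box units.
2. For (b), identify box units by unit and not by location, because Intervention description {11a} and section {11b} allow the box transfusion to finish in hospital.
3. Report both versions and name one as the main one.
4. Keep total use including box units, and whole-blood units, as descriptive summaries by arm for resource use. Do not model whole-blood units.

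**Cost.** This is mainly wording. Plans for assessment and collection of outcomes {18a} already records the donation number and start time of each unit given pre-hospital; box units started after arrival would have to be matched through the transfusion laboratories' traceability records. There are two small downsides. The box dose received is itself post-randomisation and may differ between the arms (the Discussion describes whole blood as faster to give), so version (b) is not free of bias. Version (a) rejected in 5% to 11% of null simulations, so its standard errors need a check. This is why both should be shown.
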